### Study variables

Our independent variables include:

Age: Calculated as difference between enrolment date and the date of birth for people who will participate in the study.Gender (Nominal variable): Male/Female.Education (Ordinal variable): Total number of years of education.Self-reported underlying health condition (Binary variable: yes/no): An underlying health condition is a chronic or long-term illness, which in turn weakens the immune system.Self-reported weight (kg): The body weight for each respondent in our data set measured in kilogram.Self-reported height (cm): The body weight for each respondent in our data set measured in centimeter.Place of residence: The province where people live.Exact date of pervious vaccinations.

Other main variables of the present study gathered in enrollment and follow-up questionnaires is shown in Table 2.

**Table 2 Tab2:** The main variables of the study gathered in enrolment and follow up questionnaires

Participant information	AESI(Body system)	Follow-up questionnaire
Subject ID	Acute cardiovascular injury(Cardiac)	Hospitalization
Subject Name	Chilblain like lesions(Dermatologic)	Hospitalization date
Phone number	Single organ cutaneous vasculitis(Dermatologic)	Discharge date
Gender	Erythema multiforme(Dermatologic)	Hospitalization reason
Marital status	Pancreatitis(Endocrine)	Hospitalization diagnostics
Birth date	Subacute thyroiditis(Endocrine)	Hospitalization report
Educational attainment	Acute liver injury(Gastrointestinal)	Hospital ID
Income level	Coagulation disorder (thromboembolism)(Hematologic)	COVID-19COVID-19-Test
Place of residence	Thrombocytopenia(Hematologic)	COVID-19 Symptom Onset Date
Pregnancy status	Vaccine-associated enhanced disease (VAED)(Immunologic)	ICU admission
Breastfeeding status	Anosmia, ageusia(Gastrointestinal Respiratory)	ICU admission Date
Name of next kin	Anaphylaxis(Immunologic)	Death
Vaccine dose ID	Acute aseptic arthritis(Musculoskeletal)	Death date
Vaccination date	Rhabdomyolysis(Musculoskeletal)	Reason of death
Vaccine brand	Acute disseminated encephalomyelitis (ADEM)(Neurologic)	Pregnancy
Chronic respiratory disease	Bell’s palsy(Neurologic)	Abortion
Chronic heart disease	Generalized convulsion(Neurologic)	Menstrual irregularities
Chronic liver disease	Guillain-Barré syndrome (GBS)(Neurologic)	
Chronic renal disease	Meningoencephalitis(Neurologic)	
Diabetes	Acute renal injury(Renal)	
Immunocompromised / Immunosuppressed	Acute respiratory distress syndrome(Respiratory)	
Obesity		
Allergy		
Prior Covid		
Date of Prior Covid		
History of reaction to vaccination		
Weight(Kg)		
Height(Cm)		

### Exposure of interest

The exposure of interest is either the first or second booster vaccination with AstraZeneca after the primary vaccination with Sinopharm or Sputnik V. The COVID-19 vaccine brand, dose, vaccination date and batch number will be recorded.

### Study outcomes

#### Serious adverse events (SAEs): hospitalization, death

Serious adverse events (SAEs) is defined as any over-night hospitalization or death. SAEs that lead to in-patient hospitalizations will be reported by the participant or their next of kin, and SAEs that results in death will be reported by their next of kin [12].

#### Adverse events of special interest (AESI) resulting in hospitalization

According to the WHO’s protocol template, the list of AESIs (Table 2) comprises events that have a proven relationship with immunization or a theoretical concern according to immunopathogenesis of COVID-19 disease [12].

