#### Specific objectives

To Estimate the incidence of different types of serious adverse events (SAEs) within 13 weeks in all enrolled vaccinated individuals after either the first or second booster vaccination with AstraZeneca.To estimate the incidence of different types of adverse events of special Interests (AESIs) within 13 weeks.To estimate the incidence of COVID-19 after either the first or second booster dose of A in all enrolled people.

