### Sample size estimation

Regarding the WHO’s protocol, the sample size required to rule out an event with a frequency of 1 per 3,333 with a 95% confidence interval is 10,000 per vaccine [11]. Therefore, we are planning to include 20,000 and 10,000 eligible people with previous vaccination with Sinopharm and Sputnik V respectively. Regarding the higher proportion of immunization coverage for the Sinopharm vaccine compared to Sputnik V in Iran, we will include more vaccinated people with the Sinopharm vaccine in the present study. Participants will be considered to have completed the study when they have completed the last questionnaire 13 weeks after the booster dose. The end of the study is defined as the point at which the last subject enrolled has reached the 3 months follow-up period. In this study, convenience sampling will be used to include eligible participants until achieving the required sample size.

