The present study can provide a first estimate of the incidence of SEAs and AESI and will give first insights into the incidence of new cases of Covid-19 among the cohort population after heterologous booster vaccination with AstraZeneca vaccine. In addition, it will help to measure the break through infection after booster vaccination.

There are some challenges in the present study. In the last years, the response rates tend to be low in population-based studies considerably [31, 32]. A low response rate might affect the representativeness of the cohort population which might have an effect on the generalizability of the incidence of SEAs and AESI in the Iranian source population.

Regarding that each individual should be followed-up for 13 weeks after either the first or second booster dose of the AstraZeneca vaccine, some participants might be lost to follow up due to a serious outcome such as severe events, hospitalization, or death. Some participants might not tend to be followed up for such a long time of 13 weeks. Also, some individuals may fail to complete the electronic questionnaire weekly because of poor access to a smartphone or forgetfulness. For participants who do not complete the electronic questionnaire regularly, the cohort vaccinators will contact them and fill out the follow-up questionnaire.

One of the major concerns is related to the new coming information regarding the safety of the AstraZeneca and the side effects which might lead to the AstraZeneca refusal among the cohort population [33]. This may in turn decrease our chance to reach the predefined sample size of our study.

Currently, we face remarkable low coverage of third or/and fourth doses of COVID-19 vaccine among the general population in Iran. To date (June 21, 2022), 27,685,680 people have received the third dose of the COVID-19 vaccine, while the amount for the second dose is 57,959,218. Given the notable decreasing trend of the first and second booster doses of vaccination, we might achieve the study sample size (30,000 people) within a longer period of time.

In addition, we will not monitor reactogenicity for either the first or the second booster dose of the AstraZeneca vaccine. In the present study, we just aim to investigate the SAEs (hospitalization, death), AESIs that result in hospitalization, and severe COVID-19 disease.

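### The AESI outcome is tied to hospitalization in two places and left unrestricted elsewhere, so a listed event that is fatal before admission falls outside the AESI count as written, although it remains an SAE

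*Protocol article*

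**What the plan says.** The Study outcomes section of the protocol article has a subsection headed "Adverse events of special interest (AESI) resulting in hospitalization". The text beneath it describes how the event list was drawn up and adds no alternative for death. The Discussion repeats the limit as the study's scope: "we just aim to investigate the SAEs (hospitalization, death), AESIs that result in hospitalization, and severe COVID-19 disease". That sentence names death for SAEs and omits it for AESIs. The SAE subsection agrees on the SAE side: "Serious adverse events (SAEs) is defined as any over-night hospitalization or death".

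Other parts of the article do not carry the limit:

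- Specific objectives: "To estimate the incidence of different types of adverse events of special Interests (AESIs) within 13 weeks".
- Statistical analysis: proportions, observed-to-expected comparisons and the SIR are planned for AESIs with no condition on admission.
- Subject recruitment and follow up: maternal death, neonatal death and infant death are on the list of maternal AESIs.

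Deaths are captured: "SAEs that results in death will be reported by their next of kin", and Table 2 includes a field for "Reason of death". University committees confirm diagnoses for all SAEs and AESIs, and a national committee also discusses the files.

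**The concern.** Table 2 lists events that can kill before a patient reaches a ward, such as acute cardiovascular injury, thromboembolism and anaphylaxis. Under the outcome heading and the Discussion sentence, such a death is an SAE but not an AESI. Under the objective and the analysis section, it could be counted as an AESI. Two analysts following the same article could therefore classify the same death differently.

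If the hospitalization limit is applied, the error runs toward apparent safety, and it is larger for events that more often kill before admission. It bears on the second specific objective, the incidence of each type of AESI, and possibly on the SIR. The expected counts are small enough for a single classification decision to matter, because the sample size is justified by what can be ruled out when no events are seen.

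**Working it through.** **1. Reproduce the plan's figure.** Sample size estimation states that "the sample size required to rule out an event with a frequency of 1 per 3,333 with a 95% confidence interval is 10,000 per vaccine".

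- Rule of three: n = 3/p with p = 1/3,333 gives 9,999.
- Exact zero-event form: n = ln(0.05)/ln(1 - p) = 9,983.
- The two-sided version, ln(0.025)/ln(1 - p), gives 12,293 and does not match.

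The figure of 10,000 is therefore the one-sided 95% zero-event calculation. It does not depend on how an AESI is defined.

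**2. Effect of one case on what can be ruled out.** The inputs are the planned strata, 10,000 Sputnik V and 20,000 Sinopharm, taken at full size with no loss to follow-up. Bounds are exact (Clopper-Pearson). For zero events the one-sided upper limit is 1 - 0.05^(1/n). For one event it is the p that solves (1 - p)^n + n·p·(1 - p)^(n-1) = 0.05.

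| Stratum | Events scored | One-sided 95% bound | 1 per 3,333 ruled out? |
|---|---|---|---|
| Sputnik V, 10,000 | 0 | 1 per 3,339 | yes |
| Sputnik V, 10,000 | 1 | 1 per 2,108 | no |
| Sinopharm, 20,000 | 0 | 1 per 6,677 | yes |
| Sinopharm, 20,000 | 1 | 1 per 4,216 | yes |

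The two-sided exact limits for one event are 1 per 1,795 (n = 10,000) and 1 per 3,590 (n = 20,000), which lead to the same conclusions. Leaving one pre-admission death unscored therefore preserves a claim in the Sputnik V stratum that would fail if it were scored. In the Sinopharm stratum the claim stands either way.

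**3. Effect on incidence and SIR.** Let f be the share of cases of a given AESI that die before admission. Scored incidence = true incidence × (1 - f). The SIR is multiplied by the same 1 - f only if the expected count includes pre-admission deaths. The documents do not give f; 1% to 20% is an assumed range. The last two columns take a true rate of 1 per 3,333, at which 30,000/3,333 = 9.0 cases are expected in the whole cohort.

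| f (assumed) | True SIR of 2.0 appears as | P(at least 1 scored in 10,000) | Unscored of 9.0 |
|---|---|---|---|
| 0 | 2.00 | 95.0% | 0 |
| 1% | 1.98 | 94.9% | 0.09 |
| 5% | 1.90 | 94.2% | 0.45 |
| 10% | 1.80 | 93.3% | 0.9 |
| 20% | 1.60 | 90.9% | 1.8 |

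The SIR column is 2.0 × (1 - f). The probability column is 1 - [1 - (1 - f)/3,333]^10,000. If the background rates cover admitted cases only, the SIR compares like with like and its column does not apply. The loss in absolute AESI incidence remains.

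**The case against.** A reader might infer that a fatal AESI can never be scored and that the most severe events disappear from the safety results. The documents do not support that, for four reasons.

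- The limit appears in a heading and one Discussion sentence. The objective and every analysis sentence lack it, and the maternal list counts deaths as AESIs. This is an inconsistent definition, not a settled exclusion.
- Only deaths before admission are affected. A fatal AESI that was admitted still counts.
- A pre-admission death is not lost or left unexplained. The first specific objective estimates SAEs by type, the reason for death is recorded, committees confirm the diagnosis, and observed-to-expected analysis is planned for SAEs as well as AESIs.
- The size of any bias cannot be derived from the documents. The share f is unknown, and many Table 2 events (Bell's palsy, subacute thyroiditis, chilblain-like lesions) are rarely fatal, so a high f would be implausible for most of the list. The source of the background rates is left open.

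It can also be said that this is a condensed article, that its AESI outcome follows a WHO template not shown here, and that one missed case from any cause would move the Sputnik V bound just as far.

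All of this narrows the point without removing it. Detailed case definitions may sit in the full protocol, but the article itself states two different scopes for one outcome. The planned cause-of-death data and committee review make the cases identifiable; they do not say which tabulation the cases belong to. An SAE analysis that also contains other deaths and admissions is a weaker place to see an excess of one specific AESI.

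**Conclusion.** The point holds as an inconsistency in the AESI definition with a limited consequence. As written in the outcome heading and the Discussion, a Table 2 event that is fatal before admission is outside the AESI count while remaining a reviewed SAE. AESI incidence is then low by the factor 1-f. Over the assumed 1% to 20% that is a 1% to 20% understatement, and the SIR shares it only if the background rates include such deaths. The number of cases is probably small.

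The consequence for ruling out 1 per 3,333 is confined to the Sputnik V stratum, and it assumes that the unscored death would have been the only case of its type there. It would be wrong to extend it to the Sinopharm stratum or to call a single case a safety signal. One case in 10,000 means only that the planned bound is not met.

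**What to change.** Use one AESI definition throughout: an AESI resulting in overnight hospitalization or death, the same threshold already used for SAEs. Apply it in Specific objectives, Subject recruitment and follow up (the maternal list), Study outcomes, Statistical analysis and the Discussion.

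- Assign out-of-hospital deaths to a specific AESI from the recorded reason for death and the committee review.
- Report these cases on a separate line as well as in the total, because cause of death is less certain outside hospital.
- State that background rates will follow the same case definition, so that fatal cases without admission are in both the observed and the expected counts.

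The definition costs a few words and needs no new participant data, since the cause-of-death field and committee review are already planned. The extra work is in finding background rates that include out-of-hospital deaths. Where none exist for an AESI, compute its SIR on admitted cases only, label it so, and give absolute incidence under the full definition.

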### Study period

The time point for enrolment will be either the first or second booster vaccination with AstraZeneca in one of the study sites, after primary vaccination with Sinopharm or Sputnik V.

Each individual will be followed-up for 13 weeks after either the first or second booster vaccination with AstraZeneca vaccine. Thirteen weeks follow-up period was chosen because this covers the most common risk windows for AESIs (42 days).

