### Statistical analysis

In the present study, the data on SAEs and AESIs will be included for the whole cohort population. People who do not report any event(s) will be considered as participants without event(s). As AESIs can occur even after 42 days following the first booster dose, the sensitivity analysis will be done excluding those AESIs occurring within the first 12 days after the second booster dose.

We will calculate the frequency and proportion of participants reporting AESIs and SAEs by time since vaccination. For the proportions, 95% confidence intervals will be calculated using an exact method.Observed-to-expected analyses will be conducted for SAEs and AESIs with an unknown risk window (most likely situation). The observed incidences for AESIs will be compared with background rates from the most appropriate sources. The expected rate will be age-stratified, and the standardized incidence ratio (SIR) will be calculated.Incidence rate of severe COVID-19 disease (any COVID-19 disease diagnosed by a healthcare professional, laboratory-confirmed COVID-19, hospitalization for COVID-19, COVID-19 requiring intensive care unit (ICU) admission, COVID-19 disease resulting in death) will be calculated after either the first or the second booster dose of the AstraZeneca and within the period of follow-up.

The present study will be performed in line with the international ethical guidelines for epidemiology studies published by the Council for International Organizations of Medical Sciences (CIOMS), the Declaration of Helsinki and its amendments, good epidemiological practice (GEP) guidelines and the Iran National Committee for Ethics in Biomedical Research. Data protection and privacy regulations will be strictly observed in capturing, forwarding, processing, and storing individuals’ data. The study protocol and informed consent forms will be reviewed and approved by the Iran National Committee for Ethics in Biomedical Research.

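### Hospitalized events caused by COVID-19 during follow-up enter the observed-to-expected count, so a difference in virus circulation between cohort and background source can inflate or mask the SIR.

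*Protocol article*

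**What the plan says.** All places are in the Protocol article.

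- **Basis of the AESI list** (Adverse events of special interest resulting in hospitalization): the list "comprises events that have a proven relationship with immunization or a theoretical concern according to immunopathogenesis of COVID-19 disease". Table 2 (Study variables) includes acute respiratory distress syndrome (ARDS), thromboembolic coagulation disorder, acute cardiovascular and renal injury, and the entry "Vaccine-associated enhanced disease (VAED)(Immunologic".
- **SAEs** (Serious adverse events): every overnight hospital stay and every death counts, with no exception for COVID-19.
- **COVID-19 as an outcome** (Specific objectives; Statistical analysis): COVID-19 is expected in the same cohort. Its admissions, intensive care stays and deaths are reported as an outcome of their own.
- **Analysis** (Statistical analysis): SAE and AESI data are taken for the whole cohort. Observed-to-expected analysis is planned for those whose risk window is not known, which the section regards as the usual case. "The observed incidences for AESIs will be compared with background rates from the most appropriate sources". Expected rates are stratified by age. The one sensitivity analysis is a timing exclusion unrelated to infection.
- **Data available** (Table 2; Sever COVID-19): the follow-up questionnaire records a COVID-19 test and "COVID-19 Symptom Onset Date", and COVID-19 is asked about throughout follow-up.

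**The concern.** An SIR against external rates reads as a booster effect only if everything else that causes the event acts equally on the observed and expected sides. For part of this list SARS-CoV-2 infection is such a cause, and its frequency changes with calendar time. Age stratification does not correct for that.

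The overlap shows in the protocol's own definitions. Its definition of severe COVID-19 includes severe respiratory distress, and ARDS is an AESI. A COVID-19 admission or death is both an SAE and a COVID-19 outcome.

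If the cohort meets more infection than the background source reflects, the SIR rises without any vaccine effect. If it meets less, a real excess is diluted. The reports go to the health ministry, the regulator and the immunization programme, so either error could reach policy.

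VAED is a separate, smaller matter. An event that is vaccine-associated by definition has no background rate, so an observed-to-expected ratio for it has no denominator.

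**Working it through.** **1. The plan's own figure.** The protocol states that "the sample size required to rule out an event with a frequency of 1 per 3,333 with a 95% confidence interval is 10,000 per vaccine". The zero-event bound gives n = ln(0.05)/ln(1 − 1/3,333) = 9,983, and 3/10,000 = 1/3,333. The figure reproduces, and this point does not affect it.

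**2. Inputs from the documents.** "we are planning to include 20,000 and 10,000 eligible people with previous vaccination with Sinopharm and Sputnik V respectively", so 30,000 in total. "Each individual will be followed-up for 13 weeks after either the first or second booster vaccination with AstraZeneca vaccine". With no loss to follow-up: 30,000 × 91/365.25 = 7,474 person-years.

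**3. Inputs assumed, because the documents give none.**
- Background rate without COVID-19: 20, 100 or 500 per 100,000 person-years.
- COVID-19 attack rate over 13 weeks, *a*: 1% to 10%.
- Risk of the hospitalized event per infection, *r*: 0.05% to 0.5%.

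**4. Formulas.** E = background rate × 7,474. COVID-19-caused events C = 30,000 × *a* × *r*. With true rate ratio RR, the mean observed count is O = RR × E + C, and SIR = O/(expected count used). A signal means that the exact 95% lower Poisson limit of the SIR exceeds 1.

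**5. Inflation: no vaccine effect (RR = 1), COVID-free background rates.** Each cell gives the SIR and the chance of a false signal. With C = 0 that chance is about 2%.

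| *a*, *r* | C | 20/100,000 (E = 1.49) | 100/100,000 (E = 7.47) | 500/100,000 (E = 37.37) |
|---|---|---|---|---|
| 1%, 0.05% | 0.15 | 1.10; 3% | 1.02; 2% | 1.00; 2% |
| 5%, 0.2% | 3.0 | 3.01; 47% | 1.40; 17% | 1.08; 6% |
| 5%, 0.5% | 7.5 | 6.02; 94% | 2.00; 63% | 1.20; 20% |
| 10%, 0.5% | 15.0 | 11.03; >99% | 3.01; 98% | 1.40; 59% |

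**6. Masking: RR = 2, *r* = 0.5%, reference period with 5% attack rate, cohort with 1%.** The expected count used is E + 7.5, and observed is 2E + 1.5. Power without COVID-19 on either side is in brackets.
- 100/100,000: 16.45/14.97 = 1.10; power 5% (63%).
- 500/100,000: 76.24/44.87 = 1.70; power 98% (99.8%).

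**7. Matched reference: *a* = 5%, *r* = 0.5% on both sides, 100/100,000.**
- RR = 1: 14.97/14.97 = 1.00, so the bias is gone.
- RR = 2: (14.95 + 7.5)/14.97 = 1.50. The effect is diluted but still visible.

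**8. Wrong pairing: post-COVID events removed from observed only, rates as in step 7.** The small loss of person-time is ignored.
- RR = 1: 7.47/14.97 = 0.50.
- RR = 2: 14.95/14.97 = 1.00, so a doubled risk looks like none.

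**The case against.** The strongest reply is that a condensed article has left the reference rates open. The sentence on background rates would allow a source matched on calendar period, and step 7 shows that this removes the bias when there is no effect. This stands in part. The article does not prescribe a mismatch. It does state the numerator (whole cohort), the stratifier (age) and the only sensitivity analysis, and none of these deals with infection.

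A second reply is that university and national committees review every SAE and AESI and judge its association with the booster, and that COVID-19 outcomes are reported beside the SIR, so a wave would be seen. That helps interpretation. But no text ties the committees' decisions to the observed count, and if rejected events were dropped from that side alone, the error in step 8 would follow.

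Third, AESIs count only if they lead to hospitalization. That shrinks the problem for anosmia or ageusia. It does not remove it for ARDS, thromboembolism or COVID-19 admissions.

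A reader might infer more: that every AESI and SAE goes into the SIR, or that for these events the SIR simply measures circulating virus. The documents do not support either. Observed-to-expected analysis is limited to events whose risk window is unknown, and the sentence on background rates names AESIs only. No text assigns VAED an SIR; it is simply not excluded. The large ratios in step 5 arise only when all-cause observed counts are set against COVID-free rates, a pairing that the protocol permits but does not specify.

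**Conclusion.** The point holds in conditional form. As written, hospitalized events caused by COVID-19 enter the observed count, and nothing stated on the expected side ensures the same COVID-19 content. The SIR for these events can then be inflated or masked.

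The size rests on attack rate, event risk per infection, background rate and reference period, none of which the document gives. Within the assumed ranges and with no vaccine effect, the SIR is 1.1 to 11 at 20 per 100,000 person-years, 1.02 to 3.0 at 100, and 1.00 to 1.4 at 500. The effect is negligible when infection is rare or the event is common, and large for rare events during a wave. In the masking example at 100 per 100,000, power for a true doubling falls from 63% to 5%. These figures show what could happen; they do not predict this cohort's results.

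This is worth settling before the background rates are chosen. It does not touch the sample size or the planned proportions with exact intervals.

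**What to change.** In Statistical analysis, use the COVID-19 test and symptom-onset date already collected, and report the SIR in two ways:

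- **(a) All events**, against background rates matched on calendar period or COVID-19 level. State the source's period.
- **(b) Sensitivity analysis**: events and person-time censored at COVID-19 onset, against COVID-free rates, for example pre-pandemic ones. State how a positive test without an onset date is dated.

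State that infection-free observed counts are never paired with all-cause rates that include COVID-19, and that a signal is interpreted only after (a) and (b) have been compared. Both are needed: (a) is diluted by shared COVID-19 events (step 7), while (b) depends on infections being recognized and on older rates still applying. Once person-time is censored at onset, no separate look-back window is needed for infections during follow-up.

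Report VAED as a count and as a share of COVID-19 cases, outside the observed-to-expected analysis.

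**Cost:** analysis-plan wording and one extra tabulation, with no new data collection. Analysis (b) has fewer events and less person-time, and suitable COVID-free rates must be found.
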